### Sample Size

The primary objective is to assess the effect of the interventions on their ability to improve measles vaccination coverage by an absolute difference of 15 percentage points at 10 months of age as compared with the control arm (eg, 70% measles coverage in the control arm and 85% coverage in an intervention arm). This effect size was selected because it represents a meaningful public health impact and could motivate decision makers to adopt this intervention. Data for the sample size calculation come from the M-SIMU trial; where we found a measles vaccination coverage of 70% at 10 months of age in control arm children [15]. Assuming a 70% outcome in the control group, an absolute 15% difference in the primary outcome between control and intervention arms, a type 1 error (alpha) of .05 and a power (1-beta) of 0.80, we calculated that 134 caregivers are needed in each study arm. Adjusting our sample size for a 25% loss to follow-up (death, outmigration, verbal report of measles vaccination at 10 months of age, and other reasons), our adjusted sample size is 179 participants per study arm, yielding a total sample size of 537 caregivers across the 3 study arms.

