### Setting and Participants

The M-SIMI study will take place within the boundaries of the Kenya Medical Research Institute (KEMRI) and the Centers for Disease Control and Prevention (CDC) Health and Demographic Surveillance System (HDSS) in Siaya County, Kenya. The rural study site has high levels of malaria, tuberculosis, and HIV transmission [20]; the majority of residents are subsistence farmers; and approximately 50% of caregivers own a mobile phone [21]. Data from the control arm of our previously conducted RCT found that 98% and 51% of children received pentavalent and measles vaccination by the age of 12 months, respectively [15].

The HDSS has served as a platform for numerous studies, including the M-SIMU trial, which provided text message reminders and conditional mobile-money incentives for pentavalent and measles vaccinations [15]. Potential caregivers and their children will be identified by community health workers (CHWs). CHWs are a component of Kenya’s national community health strategy and typically have a catchment area of 1 village, where the CHW visits each household at least once a month to provide minimal health services and education. Community interviewers (CIs) hired by the project will approach CHW-identified caregivers to describe the study and screen caregivers for their eligibility on the following criteria (see Textbox 1).

Caregivers will be enrolled into the study independent of mobile phone ownership. Caregivers only need to have access to a mobile phone, where access will be defined by the participant. If a caregiver cannot identify an accessible mobile phone, CIs will relay text message reminders and incentives to the participant. Caregivers will neither be provided a mobile phone nor airtime.

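### The sample size assumes 70% control coverage at 10 months, yet the same prior control arm is reported at 51% by 12 months; both cannot hold, so the stated 80% power is unsupported

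*Protocol article*

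**What the plan says.** The Sample Size section names its source ("Data for the sample size calculation come from the M-SIMU trial") and the planning value: "we found a measles vaccination coverage of 70% at 10 months of age in control arm children". The target is an absolute gain of 15 percentage points, illustrated as "70% measles coverage in the control arm and 85% coverage in an intervention arm". With "a type 1 error (alpha) of .05 and a power (1-beta) of 0.80", the authors write that "we calculated that 134 caregivers are needed in each study arm". Allowing for 25% loss, they arrive at 179 per arm and 537 in total. The Results section reports that 537 were enrolled and that the sample size requirement was met.

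The Setting and Participants section describes the background rate differently. It begins "Data from the control arm of our previously conducted RCT found that" and continues "98% and 51% of children received pentavalent and measles vaccination by the age of 12 months, respectively". Both statements carry citation 15, which the Introduction and the Setting section identify as M-SIMU.

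**The concern.** The two statements share the trial, the arm, the vaccine and the citation. A child vaccinated by 10 months is also vaccinated by 12 months, so the later figure must be at least as large as the earlier one. Here it is 19 points smaller (70 − 51). Nothing in the article gives a different denominator, subset, definition or estimation method that would explain the drop.

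This matters because 70% is the only event rate in the calculation. A proportion is most variable near 50%, so a control rate of about 51% or lower makes the same 15-point difference harder to detect. The article chose 15 points as the effect that could persuade decision makers to adopt the intervention. If power for that effect is well below 80%, a non-significant result is weaker evidence against it than the stated design suggests.

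**Working it through.** **Inputs from the article.** Control 70%, intervention 85%, alpha 0.05, power 0.80, 134 evaluable per arm, 25% loss, 179 enrolled per arm (all Sample Size); control 51% by 12 months (Setting and Participants); 1:1:1 allocation (Study Design). Sidedness is not stated; a two-sided test reproduces the stated number.

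**Formulas.** With d = p2 − p1 and p̄ = (p1 + p2)/2:

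- Uncorrected: n = [1.960·√(2p̄(1−p̄)) + 0.842·√(p1(1−p1) + p2(1−p2))]² / d²
- Continuity-corrected: n_c = (n/4)·[1 + √(1 + 4/(n·d))]²
- Power: Φ{[d − c − 1.960·√(2p̄(1−p̄)/n)] / √[(p1(1−p1) + p2(1−p2))/n]}, with c = 1/n if corrected and 0 if not

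**Step 1: reproduce the plan (70% v 85%).** p̄ = 0.775; the two square roots are 0.5906 and 0.5809.

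- n = (1.960 × 0.5906 + 0.842 × 0.5809)² / 0.0225 = 120.5
- n_c = 133.5, rounded up to 134, as stated
- 134 / 0.75 = 178.7, rounded up to 179, as stated
- Power at 134: 80% corrected, 84% uncorrected

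The plan therefore used the continuity-corrected formula and applied it correctly.

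**Step 2: use 51% as the control rate (51% v 66%).** This is the highest 10-month rate compatible with 51% by 12 months. p̄ = 0.585; the square roots are 0.6968 and 0.6887.

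- n = (1.960 × 0.6968 + 0.842 × 0.6887)² / 0.0225 = 168.2, so 169
- n_c = 181.3, so 182; 182 / 0.75 = 242.7, so 243 enrolled per arm against 179
- Power at 134: 66.0% corrected, 70.5% uncorrected
- Difference detectable with 80% power at 134 per arm: 17.5 points corrected (15.0 at 70% control), 16.7 uncorrected (14.3 at 70% control)

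**Step 3: vary the control rate, keeping a 15-point difference.** Rates other than 51% and 70% are assumptions.

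| Control coverage at 10 months | Evaluable n per arm for 80% power, corrected (uncorrected) | Power at 134, corrected (uncorrected) | Power at 179, corrected (uncorrected) |
|---|---|---|---|
| 40% | 186 (173) | 65% (69%) | 78% (81%) |
| 45% | 186 (173) | 65% (69%) | 78% (81%) |
| 51% | 182 (169) | 66% (70%) | 79% (82%) |
| 60% | 165 (152) | 70% (75%) | 83% (86%) |
| 70% | 134 (121) | 80% (84%) | 91% (93%) |
| 75% | 113 (100) | 87% (90%) | 95% (96%) |

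Between 40% and 51% the answer hardly moves. The exact 10-month rate therefore matters little in that range if the 51% is right.

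**The case against.** The strongest reply is that the documents do not show the trial to be underpowered. The 51% appears in a background sentence and may be a slip, or may describe a subset or a stricter definition. In that case 70% stands, and so does the 80%. This is fair: every power loss given here is conditional on the 51%. It does not remove the contradiction, because the article states both figures for the same control arm without qualification.

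Second, the sample size arithmetic contains no error. That is also right; the fault lies in an input that another section contradicts.

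Third, the 66–70% assumes the full 25% loss. Verbal reports are counted in that loss, but the Outcomes section adds a facility registry search for such cases and says over 95% of caregivers had a booklet in the earlier study. Loss may therefore be smaller. At 51% v 66%, power would be 75–78% with 10% loss (161 per arm), 77–80% with 5% loss (170) and 79–82% with none. This softens the consequence but gives up the plan's own allowance.

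Fourth, a null result is judged by the estimate and its precision rather than by planned power, and enrolment is complete. Both are true. They limit the remedy to correcting the record, but the article still relies on the figure when it reports that the sample size requirement was met.

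**Conclusion.** The point holds: as written, the two coverage figures cannot both be right, and the stated 80% power rests on the one that the other contradicts. "Unsupported" is the right description of the power; the article does not establish that it is wrong. This assumes that both figures refer to the same children and count vaccination by age in the same way, as the shared arm and citation imply.

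If the 51% is correct, power for a 15-point difference at the planned 134 evaluable per arm falls from 80% to about 66% with continuity correction, or from 84% to about 70% without it. About 80% returns only if nearly all 179 per arm are evaluable. If the 70% is correct, the sample size stands and only the Setting and Participants section needs correction.

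**What to change.** Re-extract control-arm measles coverage by 10 and by 12 months from the prior trial's data. State the denominator, the definition and the source of the vaccination record for each, and correct or explain whichever section is wrong.

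If 70% is confirmed, correct the 51% in Setting and Participants and leave the sample size as it is. If 51% stands, restate power as about 66–70% at 134 evaluable per arm, or the difference detectable with 80% power as about 17 points, and add a short table over control coverage of 40–75% such as the one above. State that the calculation is two-sided and continuity-corrected, so that readers can reproduce it.

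The cost is a check of data the team already holds and a few sentences. No change to enrolment, randomization or analysis is needed. The only drawback is that the stated power may look less favourable.

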### Ethical Considerations

This study protocol received ethical clearance from the Scientific Steering Committee, the KEMRI Scientific and Ethics Review Unit (SERU; KEMRI/SERU/CGHR/003/3311; Multimedia Appendix 1), and the Johns Hopkins University Bloomberg School of Public Health (deferred ethical clearance to KEMRI-ERC). All participants will provide written informed consent. If a participant is illiterate, consent forms will be administered and signed in front of an impartial witness. At the 12-month household visit, study staff will refer the caregivers of unvaccinated children to the nearest health facility that provides measles vaccination.

## Results

M-SIMI completed enrollment in March of 2017. We met our sample size requirement and enrolled 537 caregivers and their infants into the following groups: control (n=179), SMS reminders only (n=179), and SMS reminders plus 150 KES (n=179). Results will be made publicly available in 2020.

## Discussion

### Differences Between Previous Studies

This proposed study differs from our previous cluster RCT, the M-SIMU study, in several ways [15,19]. First, M-SIMU enrolled infants younger than 5 weeks and provided reminders and incentives for the pentavalent vaccine series at 6, 10, and 14 weeks of age and for measles vaccine at 9 months of age. The significant effect of incentives on measles coverage may be due to caregivers previously receiving travel subsidies and reminders for the 3 pentavalent doses. Contrastingly, the M-SIMI study seeks to enroll caregivers of children aged 6 to 8 months and to provide reminders and unconditional travel subsidies only for measles vaccination.

A second difference, and perhaps a more important one, is that M-SIMU provided conditional incentives for vaccination, where the incentive was only given if the caregiver brought their child for vaccination within 2 weeks of the EPI due date. M-SIMU–employed health facility recorders were stationed at each clinic to confirm a timely vaccination. With busy clinic workers, this conditional approach is difficult to scale because it requires staff at the clinic to document immunization and to calculate whether the immunization was received in time. To counter these logistical and implementation challenges, the M-SIMI trial will provide an incentive unconditionally, that is, the caregiver receives an incentive 3 days before the child’s 9-month birthday and independent of whether the child has been vaccinated for measles.

A third difference between M-SIMU and M-SIMI is in the enrollment strategy. Where the M-SIMU trial employed KEMRI HDSS village reporters to identify births and deaths, this proposed study seeks to leverage CHWs, a component of Kenya’s national community health strategy, to identify and enroll children into a travel subsidy scheme. Village reporters are a unique component of the HDSS, making the external generalizability of our results somewhat limited, whereas numerous countries have national CHWs.

### Limitations

This study has several potential limitations. First, not all caregivers will provide written immunization records at the 12-month follow-up visit. Evidence from other settings implies that they may under or overestimate actual vaccination coverage [24-26]. It is likely that social desirability bias may lead those who received an incentive in this study to verbally report vaccination. At the same time, this bias may be minimal as the M-SIMU trial found that over 95% of caregivers had an MCH booklet at 12 months of age [15]. An additional limitation of this study is that the CIs who will collect measles vaccination status at the follow-up visit will also be responsible for assigning the study arm at enrollment (ie, not blinded to study arm allocation). To minimize the risk of outcome ascertainment bias, the follow-up questionnaire will be structured to collect vaccination data before any questions that identified the study arm allocation. For CIs to be biased when ascertaining vaccination status, they would have had to rely on their memory of the participant’s study arm allocation during the enrollment visit, which was conducted 4 to 6 months before the follow-up visit.

We hypothesize that the interventions will improve measles vaccination coverage and that they will be effective in many of the traditionally hard-to-reach populations. By designing this study with scalability in mind, the results of this trial will hopefully approximate the effects of national or subnational programs.

## Appendix

Multimedia Appendix 1 Center Scientific Committee review comments.

## Abbreviations

CDC: Centers for Disease Control and Prevention
CHW: community health worker
CI: community interviewer
EPI: Expanded Program on Immunization
HDSS: Health and Demographic Surveillance System
KEMRI: Kenya Medical Research Institute
KES: Kenyan Shilling
LMICs: low- and middle-income countries
MCH: maternal and child health
M-SIMI: Mobile and Scalable Innovations for Measles Immunization
M-SIMU: Mobile Solutions for Immunization
RCT: randomized controlled trial
SMS: short message service
